## Discussion

This study describes an RCT of a web-based nutrition education programme. Promoting vegetable intake is an important challenge for health promotion during adulthood, regardless of socio-economic status. Japanese adults of all household income levels consume less than approximately two-thirds of the recommended daily amount (i.e. 350 g or five servings per day). Support for the increased intake of appropriate vegetables seems best implemented using a population-based approach, as this issue is necessary for not only lower-income groups, but also the entire adult population. Web-based nutrition education programmes are communication tools that use ICT, in particular the Internet. In other words, it is a health education tool for which future expansion can be anticipated in fields of health promotion. If we could show that such web-based nutrition education programmes are beneficial for improving vegetable intake, our population-based approach would enable lower-income groups to catch up in terms of averaged daily intake of vegetables while also contributing to the resolution of the overall deficiency in vegetable intake in Japan’s overall adult population. So far as we know, this is the first report regarding a web-based nutrition education programme developed with a focus on socio-economic status.

### Strengths and limitations

This study has three main strengths. First, this is an RCT using high-quality research methods. Because the RCT participants were assigned randomly, there is very little allocation bias. Additionally, randomization took place after acquiring consent to participate, which means that the intervention group was not populated only with participants actively interested in the research topic. This helps in avoiding over-estimation of the effects of the nutrition education programme in the intervention group. Second, this is nutrition education programme was web-based, thus making it highly accessible. Furthermore, the study was carried out by a social research company with a wealth of experience in implementing academic research surveys. These points ensured high feasibility while minimizing the burden of securing an adequate sample size to increase statistical power. In addition, participants could be extracted to match the distribution of sex and age in the Basic Resident Register and household income in the Comprehensive Survey of Living Conditions. For this reason, possible confounding effects could for the most part be eliminated at the stage of allocation. Third, the programme affords numerous advantages for both participants and supporters. Participants can take part when they are free to do so (e.g. time, place, and scheduling). As this means that they can take part even if they are located far away from the researchers, it would be highly convenient for participants [26]. The programme also offers supporters the opportunity to provide a unified nutrition education programme that is not reliant on the number of participants and to provide support without being subject to spatial or geographical restrictions. While it is true that the initial cost is somewhat considerable, its operational costs are low. The economic burden on supporters is thus small. Furthermore, passwords can be set for browsing the nutrition education programme, which can prevent communication between groups that could impact the quality of research.

The RCT in this study is original in the following two regards. (1) It can verify the intervention effect for an adequate sample size, and (2) it can verify differences in the effect of a nutrition education programme by income strata. With this study, it will also be possible to verify the possible catch-up effect in relation to undesirable vegetable intake behaviour associated with low household income. Some reports have suggested that traditional classroom-based nutrition interventions might widen this disparity [6]. In contrast, with our study, it may be possible to show that a web-based nutrition education programme would inhibit the widening of this disparity.

Conversely, this study also has its limitations. It is possible that the results of the study will reflect the characteristics of individuals registered with the research company (e.g., tending to be young, high-earning, and highly educated [51–53]). To minimize this potential limitation, we have made sure to match participants with demographic distributions in terms of sex, age, and household income. In addition, we requested research cooperation from individuals whose household income data – which was our objective – had been recorded in advance. This helps to restrict attribute bias as well as negative response rates for delicate questions pertaining to household income and other matters. Second, during participant recruitment, we excluded individuals reporting household incomes of ten million JPY or more. This means that the results do not target the entire population. Accordingly, care must be taken when drawing general conclusions. However, a limit of less than ten million JPY still applies to 88.4% of the Japanese population. Finally, participants did not have contact with one another (either in person or through indirect communication) for the period of the intervention. For this reason, it is possible that rates of adherence to nutrition education programmes will be lower than they would with enforced participation.

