In Japan, Ministry of Internal Affairs and Communications report on Internet usage by Japanese citizens [25] shows that, today, the proportion of Internet users among all Japanese aged 30–59 is 90% or more. Furthermore, the proportion of lower-income individuals (i.e., who are earning less than two million JPY per annum; approx. 15,800 GBP) is 61%, and rising annually. A relatively high proportion of respondents to this report indicated that they use the Internet to search for information about health and medicine, ranging from 73% among 30-year-olds to 80% among 59-year-olds. The proportion of respondents who reported using the Internet at least once a week was as high as 91%. Thus, as a form of information and communications technology (ICT), the Internet is a powerful health education tool for which future expansion can be anticipated in fields of health promotion, especially nutrition [26]. Web-based nutrition education programmes by their nature rely on ICT and the Internet in particular [27]. However, in the context of web-based support for increased vegetable intake, there are almost no reports, even at the worldwide level, verifying the effects of these programmes according to income level.

In this paper, we describe the methods and protocol of a randomized controlled trial (RCT) that seeks to verify the effectiveness of a web-based nutrition education programme of promoting vegetable intake among adults and that is based on behavioural science theory. The main objective of the RCT is to develop and verify the effects of a 5-week programme of promoting vegetable intake. A secondary objective is to determine how the effects of this web-based nutrition education programme differ according to socio-economic status.

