### Intervention programme

An interactive webpage called the ‘Diet and Exercise Practices Project (http://healthpromotionqol.com)’ is designed to improve vegetable intake of visitors to help decrease the likelihood of lifestyle-related diseases (Fig. 2). It is a free website that provides information, a monitoring sheet, and advice about healthy diets, increasing vegetable intake, and preventing lifestyle-related diseases. We hypothesize that achieving an approximately 70 g (1 serving) increase in vegetable intake might help lower-income groups to catch up while simultaneously contributing to the partial resolution of the deficient vegetable intake amongst Japan’s adult population. Therefore, the action goals of intervention is a vegetable dish to eat five servings, or was a plus 1 serving (approximately 70 g) per day. The programme is divided into five steps that align with the stages of behaviour change. Table 1 shows the framework of the programme. To be updated every week, but watch the past step not proceed in the previous step. It was created to advance the based on behavioural science theory. To avoid contamination during the intervention period, access to the webpage was password-restricted so that only study participants could visit it.

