### Sample size

The sample size was calculated using G*Power [50]. We set an effect size of 0.5, an α of 0.05, and a power of 0.95. With the expectation that two-thirds of participants would drop out, the size of the intervention group was set at 900 subjects, while that of the control group was set at 600 subjects with the expectation that a half of participants would drop out. Furthermore, we aimed to divide the intervention and control groups further according to income (low and high).

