### Statistical analyses

All statistical analyses will be performed with IBM SPSS Statistics 21.0. For continuous variables, independent t-tests will be used to determine inter-group differences and Man–Whitney U-tests for intra-group comparison, while the χ^2^ or an equivalent test is to be used to determine the associations between categorical variables. Because this is a prospective RCT involving repeated measures, repeated measures analyses of variance will be applied to determine significant differences within the study groups. We also considered the possible effect of time on groups. The evaluation of the intervention is based on an intention-to-treat analysis. A *p*-value of 0.05 has been set as the level of significance.

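### The protocol says it can verify differences in effect by income, but its stated analyses name no arm-by-income contrast and its sample size addresses none

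*Protocol article*

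**What the plan says.** The end of the Background sets the objective: "A secondary objective is to determine how the effects of this web-based nutrition education programme differ according to socio-economic status". Strengths and limitations counts this among the two original features of the trial, stating that "it can verify differences in the effect of a nutrition education programme by income strata", and adds that a catch-up effect linked to low household income can be verified.

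In the methods, income enters the design of the comparison once, under Sample size: "we aimed to divide the intervention and control groups further according to income (low and high". No cut-off between low and high and no size for the resulting cells is given. The same section gives one set of planning inputs: "We set an effect size of 0.5, an α of 0.05, and a power of 0.95".

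Under Statistical analyses, "independent t-tests will be used to determine inter-group differences". Mann–Whitney tests, chi-square tests and a repeated-measures analysis of variance follow; the last is described as looking for differences inside the study groups. One further sentence mentions an effect of time on groups. Income appears nowhere in that section.

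On the size of change hoped for, the Background and Intervention programme sections say that "achieving an approximately 70 g (1 serving) increase in vegetable intake might help lower-income groups to catch up".

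**The concern.** Saying that an effect differs by income is a statement about (effect in low income) minus (effect in high income). None of the listed tests, as described, estimates that quantity. Applied to arms already split by income, a two-group test gives one result per stratum. A significant result in one stratum beside a non-significant one in the other is easily read as an income difference, although it can arise often when the two effects are equal.

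The precision of the contrast is a second matter. Sample size gives one effect size and does not mention a difference between effects, yet the Discussion claims the difference can be verified. An interaction estimate from four cells is less precise than a main effect from two arms, so precision for the main comparison does not carry over.

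The catch-up wording bears on the same contrast. The Background puts the gap between income groups at about 70 g per day, and the programme aims for about +70 g per day for everyone. Whether that closes the gap depends on whether the effect is larger in the low-income group.

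**Working it through.** **Inputs**

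- Intervention arm: "With the expectation that two-thirds of participants would drop out, the size of the intervention group was set at 900 subjects".
- Control arm: "control group was set at 600 subjects with the expectation that a half of participants would drop out".
- Effect size 0.5, alpha 0.05, power 0.95 (Sample size). The type of effect size and the sidedness are not stated; I read them as a standardised mean difference and two-sided.
- Share of low income: not given. Assumed 50:50, with 25:75 as the other end of the range.
- Normal approximation, outcome SD = 1, no baseline adjustment.

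**The plan's own figure**

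Completers are 900 × 1/3 = 300 and 600 × 1/2 = 300, so the two arms agree. The stated inputs need 105 completers per arm (315 and 210 enrolled), or 210 per arm (630 and 420 enrolled) if each of two income strata is powered separately. Neither gives 900 and 600. I use the 300 completers per arm, which is the more favourable figure for the trial; that the sample size does not reproduce is a separate matter.

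**Separate tests per stratum when the true effect is the same in both**

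With 150 completers per arm in each stratum, SE = √(2/150) = 0.1155 SD. Stratum power is p = Φ(d/0.1155 − 1.96), and the chance that exactly one stratum is significant is 2p(1 − p).

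| True effect in both strata (SD) | Stratum power p | Exactly one significant |
|---|---|---|
| 0.2 | 0.410 | 48% |
| 0.3 | 0.738 | 39% |
| 0.4 | 0.934 | 12% |
| 0.5 | 0.991 | 2% |

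An interaction test would wrongly report a difference in 5% of such trials, by its alpha.

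**The contrast itself**

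SE = √(2/n_low + 2/n_high), with n the completers per arm in each stratum.

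- 50:50 split: √(2/150 + 2/150) = 0.163 SD. The 95% confidence interval is about ±1.96 × 0.163 = ±0.32 SD.
- 25:75 split: √(2/75 + 2/225) = 0.189 SD.

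| | 50:50 | 25:75 |
|---|---|---|
| Power, difference 0.5 SD | 86.5% | 75.5% |
| Power, difference 0.3 SD | 45% | 36% |
| Power, difference 0.25 SD | 33% | 26% |
| Detectable at 80% power | 0.46 SD | 0.53 SD |
| Detectable at 95% power | 0.59 SD | 0.68 SD |

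A difference of 0.5 SD means the whole planning effect in one stratum and none in the other. A difference of 0.25 SD means the effect in one stratum is half the planning value while the other has all of it.

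To hold the plan's 95% power for a 0.5 SD interaction takes 4 × (3.605/0.5)² = 208 completers per cell, or 416 per arm. At the stated dropout that is 416 × 3 = 1248 and 416 × 2 = 832 enrolled.

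**Catch-up**

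If H and L are mean intakes and H − L = 70 g, an equal gain gives (H + 70) − (L + 70) = 70 g. The gap is unchanged. Closing it needs a larger effect in the low-income group; not widening it does not.

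**The case against.** A condensed article commonly leaves model details to a statistical analysis plan, and one may exist. The repeated-measures analysis of variance could carry income as a between-subject factor, and the sentence on time and groups shows that the authors had joint effects in mind. This stands as far as it goes: the missing model term alone would be a weak point. What it does not answer is the claim that the difference can be verified. A later plan can add a term, but it cannot supply precision that the sample size was not built to give.

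A reader might infer that the authors will compare subgroup p-values. The document does not say so. It supports only that the objective is left open to separate stratum tests.

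The discordance figures depend on the true effect. At the plan's own 0.5 SD the rate is about 2%, and power for a 0.5 SD interaction is above 80% under a 50:50 split. The risk therefore lies with effects below the planning value.

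A reader might also infer that the five-servings target will make an equal gain look like widening disparity. The document does not establish this. The Discussion frames catch-up as average daily intake, Secondary outcomes collects servings and grams per day, and the size of any distortion depends on an intake distribution that the document does not fix.

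Finally, Strengths and limitations also hopes to show that disparity does not widen, which equal gains would satisfy. So the catch-up argument applies to closing the gap only, and the authors say no more than that +70 g might help.

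**Conclusion.** The point holds. The secondary objective and the verification claim need a difference between two effects, and the stated analyses contain no income factor or contrast for it. At the expected completers and a 50:50 income split, the trial would estimate that difference to within about ±0.32 SD. That is enough to detect a very large difference and too little to verify one of 0.25 SD.

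These figures assume a standardised effect size, two-sided testing, the stated dropout and an income split that the document does not give. Baseline adjustment would narrow the interval, but no correlation is stated from which to say by how much.

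Severity is moderate. The secondary objective and one of the two claims to originality are affected; the main comparison of the arms is not.

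**What to change.** Add to Statistical analyses: effect modification by income is assessed by the arm-by-income (by time) interaction in all randomised participants, on one named continuous measure of vegetable intake already collected (servings or grams per day), adjusted for its baseline value. It is reported as the low-minus-high difference in effects with a 95% confidence interval, and effects within each stratum are descriptive. Vegetable intake is proposed because the catch-up claim concerns it.

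Also:

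- Define the cut-off between low and high income before the data are analysed.
- Separate closing the gap (a larger effect in low income) from not widening it (an effect at least as large).
- Under Strengths and limitations, replace verify with estimate for the income comparison, and give the detectable difference: 0.46 SD at 80% power under a 50:50 split, recalculated once the cut-off is set.

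The cost is one model term and some wording. No new data are needed, since household income and both intake measures are already collected. The downside is that a claim of verification becomes an estimate with a wide interval.

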### Implications for practice

The promotion of vegetable intake behaviour is an important challenge for health promotion during adulthood, regardless of socio-economic status. ‘Health Japan 21 (the second term)’ policy initiative [21] is promoting the use of ICT as a health promotion strategy for the future. Because ICT frees individuals from the limitations of time or place, it may be a tool that encompasses individuals in lower socio-economic strata who have little time to spare. If we can show that web-based nutrition education programmes have a positive effect, our study would represent the outcome of a population approach as a health promotion strategy.

## Abbreviations

ICT: Information and communications technology
RCT: Randomized controlled trial
